## Discussion

This study will be the first to apply IOT technology to monitor and control the added salt intake in Chinese households. We expect to find that the salt consumption-related KAP score will be higher and the daily added salt intake of each household member will be less in the intervention group than in the control group. In the intervention group, we also expect that the time trend of the daily added salt intake of each household member will show an overall downward trend. A stronger reduction is expected in salt over-consumption households, and the strength of the effect is expected to be higher between 3 months and baseline than between 6 months and baseline and between 6 and 3 months due to time effect [16]. We speculate that if the monitoring system is used continuously after 6 months, the salt consumption-related KAP of the household’s main cook will improve continuously or be maintained at a good level, and the daily added salt intake of each household member will decrease continuously or be maintained under the recommended level of the Chinese Nutrition Society (6 g/d) [3]. In addition, the demographic characteristics may be factors that influence the SALTCHECKER effect.

The four main advantages of this study are as follows. First, compared with similar trials aimed at reducing salt intake with simpler approaches [44–46], the SALTCHECKER in the present study could monitor the daily added salt consumption of each household member with less labour cost and more convenience, and reflect on the household’s main cook’s habit of using salt in the real-world setting. Besides, the salt-limiting WeChat programme could provide personalized suggestions to users, which may produce a better salt-limiting effect. Second, a traditional weighing method is considered to be too complicated for accurate assessment of the added salt intake of each household member, although the SALTCHECKER is less accurate, it is simple enough that residents can use by themselves [47]. Third, the system can monitor the household added salt consumption for a long time, which can reflect the habitual added salt intake of household members and reduce measurement error, compared with traditional survey methods. Fourth, as the number of smartphone users worldwide today surpasses three billion and is forecast to further grow by several hundred million in the next few years [48]. China, India, and the United States are the countries with the highest number of smartphone users, with each country easily surpassing the 100 million users [48]. Therefore, we consider a large number of smartphone users could represent a study population and the system could apply to other populous smartphone-using countries.

There are also four main limiting factors in this study. First, the method of estimating the added salt intake of each household member may not be accurate. Although we will take measures to reduce the salt consumption measurement error, we cannot ensure the salt used for cooking or at the table is taken from the salt checker container only. In addition, the salt intake may be from at-home and out-of-home sources, and the average prevalence of food away from home consumption increased from 9.40% to 13.95% between 2004 and 2011 in China [49]. Although at present, the SALTCHECKER can only measure the added salt consumption at home, we will use the salt-limiting WeChat mini programme to obtain information on participants’ dietary behaviours, such as the frequency of eating out, the places to eat, and the number of meals per day. We also hope to have a smarter and more accurate way to monitor salt intake from other sources such as out-of-home eating, ultra-processed foods and condiments containing sodium in the future. Second, we cannot ensure that all household main cooks will persist in receiving the intervention on the salt-limiting WeChat mini programme, which may hinder the intervention effects. To address this limitation, we will send prompting text messages to the participating household’s main cook at a fixed time weekly and set a daily punch-in reminder function in the WeChat mini programme. Besides, we will provide some reward (e.g. a salt spoon with a scale, a sphygmomanometer and a smart watch) to promote adherence to the daily use of the system for the participants. All relevant data can be entered into the registry database in the WeChat mini programme flexibly and dynamically, and which the participants can view their data at any time with the Internet. Third, the salt-limiting effects may be insignificant because the planned intervention time is 6 months. Although we found that 6 months of salt-limiting intervention could have an effect in a previous study [45], we hope the intervention time will be extended and the long-term salt-limiting effects will be reflected in further research. Fourth, this study will be conducted in Chongqing, China, where the dietary habits are different from those in other places. This setting may limit generalisability, but the feasibility of the findings will inform the development of a larger effectiveness trial.

This study will provide a monitoring system for the calculation of added salt intake of each household member and guidance for salt-limiting behaviour, which can be used as a reference for similar studies elsewhere. Through the assessment of the effectiveness of SALTCHECKER, the reduction in the added salt intake of each household member and the improvement in the salt consumption-related KAP of the household’s main cook will provide an excellent way to manage and control salt intake. The system can also be easily incorporated into health management and promotion interventions.

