#### Control group

The household’s main cook in the control group will have access to the smart salt checker with only the weighing function.

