#### Data of the daily added salt intake integrity

Before the study, the participants will be informed that they will be provided with salt for free, which aims to make them use the added salt only from the smart salt checker container in the survey period. And the measured outliers will be excluded, which may be caused by using too much salt for preserving food, adding too much salt to the smart salt checker or other reasons. A certain reward will be given to the households’ main cooks who actively participate in the programme every month.

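### Support for using the salt checker is not fixed as equal by arm and, as written, appears to favour the intervention arm, so recorded salt intake could differ by arm for reasons other than intake

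*Protocol article*

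**What the plan says.** The limitations paragraph of the Discussion raises a worry about persistence: "we cannot ensure that all household main cooks will persist in receiving the intervention on the salt-limiting WeChat mini programme". Its answer is that "we will send prompting text messages to the participating household’s main cook at a fixed time weekly and set a daily punch-in reminder function". The reminder's place is explicit: the team will "set a daily punch-in reminder function in the WeChat mini programme". A separate sentence then offers rewards "to promote adherence to the daily use of the system for the participants". In the Quality control part, the section on integrity of the salt data adds: "A certain reward will be given to the households’ main cooks who actively participate in the programme every month". None of these sentences names an arm.

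The Control group section reads: "The household’s main cook in the control group will have access to the smart salt checker with only the weighing function". The Methods part of the Abstract likewise makes the mini programme the difference between the arms. The Intervention group section describes monthly reports, health education and access to nutrition experts, but lists neither prompts nor rewards.

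Under Baseline survey, the salt data come from the checker itself, and Primary outcomes makes daily added salt intake a primary outcome. The Discussion concedes that "we cannot ensure the salt used for cooking or at the table is taken from the salt checker container only".

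**The concern.** The checker is both part of what is tested and the instrument that measures the outcome. It records salt only when the cook takes it from the container, puts the container back on its base and closes the lid. Anything that encourages regular use of the checker therefore also makes the outcome record more complete.

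If that encouragement reaches mainly the intervention arm, the two arms are measured with different completeness. Intervention households that capture a larger share of their salt would show a higher recorded intake than controls with the same true intake, and a real reduction could be hidden. If prompts or rewards instead led some households to bypass the container, the bias would run the other way and suggest a benefit that is not there. Salt that never passes through the container is not recorded, so no later analysis can recover it.

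**Working it through.** **Step 1: which arm gets the support?** The protocol gives no figure for this, and its sample size calculation does not bear on it. The passages have to be set side by side.

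- *Weekly texts.* They go to the participating main cook and no arm is named. The stated reason is persistence with the intervention, which only one arm receives.
- *Daily punch-in reminder.* Same stated reason, and placed inside the mini programme. Control cooks "will have access to the smart salt checker with only the weighing function".
- *Rewards in the Discussion.* For daily use of the system, given to participants. The system may mean the whole SALTCHECKER, which the Abstract contrasts with the plain checker, or only the device.
- *Monthly reward in the data-integrity section.* For active participation in the programme, which may mean the mini programme or the study.
- *Pointing the other way.* Recruitment requires every participant to accept the mini programme on the phone. Questionnaire survey and Online questionnaire survey send the questionnaire through it without restriction by arm. Free salt is offered to participants in general.

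There are two possibilities for the reminder. If controls do not receive it, support for device use is unequal. If they do, they have more than the weighing function that the Control group section allows them. Either way the sections need to be reconciled.

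**Step 2: how could this reach the outcome?** The Development of SALTCHECKER section divides the household's 30-day recorded salt, shared among its members, by 30. Salt taken from elsewhere lowers that total while the divisor stays the same. Dividing by days of use instead would not correct for partial use within a day. If lapses were dropped as missing days, the direction of any bias could not be known.

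**Step 3: illustration of size.** The capture rates and the true intake of 6–8 g/d are assumptions; the protocol gives neither. With equal true intake in both arms,

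false difference (intervention − control) = (capture in intervention − capture in control) × true intake.

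| Capture, intervention | Capture, control | Gap | At 6 g/d | At 8 g/d |
|---|---|---|---|---|
| 95% | 90% | +0.05 | +0.3 g/d | +0.4 g/d |
| 95% | 85% | +0.10 | +0.6 g/d | +0.8 g/d |
| 90% | 75% | +0.15 | +0.9 g/d | +1.2 g/d |
| 85% | 95% | −0.10 | −0.6 g/d | −0.8 g/d |

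The last row shows the reversed case.

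Now suppose a true reduction of 10% and 95% capture in the intervention arm. Recorded intake there is 0.95 × 0.90 = 0.855 of true control intake. Subtracting control capture gives the recorded difference, in percentage points of true control intake:

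- control capture 95%: 0.855 − 0.95 = −9.5
- control capture 90%: 0.855 − 0.90 = −4.5
- control capture 85%: 0.855 − 0.85 = +0.5
- control capture 80%: 0.855 − 0.80 = +5.5

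On these assumptions, a gap of 10 points is enough to make a true 10% reduction disappear.

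**The case against.** The strongest reply is that the protocol never assigns a prompt or reward to one arm. A reader might infer that all prompts run through the mini programme and that rewards pay for activity in it, so that measurement is plainly supported unequally. The text does not support that. The weekly prompts are text messages. The aim of daily use is attached to the rewards, not to the texts or the reminder, so the step from prompts to device use is an inference. The monthly reward stands in a section on data integrity, next to free salt for participants, where the programme may well mean the study. Controls appear to hold the mini programme at least for questionnaires and could receive the reminder there. Nor are the prompts an undeclared co-intervention: the Discussion declares them, and they may be adherence support within the tested package.

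It can also be said that a journal article commonly leaves schedules of texts and incentives to the full protocol, and that reminders to controls might change how they use salt.

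Most of this stands and limits the point. It does not remove it. The article gives a reason for the prompts that applies to one arm, puts the reminder in the component that separates the arms, and describes controls as having only a weighing function. That is a tension between stated passages, not merely detail left out.

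**Conclusion.** The concern holds in a limited form. On the plain reading of the Discussion together with the Control group section, adherence support that can affect outcome capture falls mainly on the intervention arm. Other sections leave open that controls share some or all of it, so inequality is likely but not established.

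If support is unequal, the between-arm comparison of recorded salt could be biased. The range of 0.3–1.2 g/d rests wholly on assumed capture gaps of 5 to 15 points and an assumed intake of 6–8 g/d. It shows what such gaps would do, not what will happen, and the sign could be the opposite. The point should be settled before the trial starts, because prevention is cheap and the loss cannot be repaired in the analysis.

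**What to change.** Reconcile the Intervention group, Control group, data-integrity and Discussion sections as follows.

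1. State each prompt and each reward by arm.
2. Send device-use prompts (use the container, replace it, close the lid) to both arms by text message, with identical, neutral wording and timing.
3. Keep prompts to read reports or articles for the intervention arm only, and list them in the Intervention group section as part of the intervention.
4. Pay rewards in both arms by one rule that both can meet: days with a valid checker reading. The rule should not depend on mini-programme activity.
5. Report device-use days by arm, so that readers can judge whether use of the checker was similar.

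The cost is text messages to the 300 control households and one shared reward rule. The downside is slightly more contact with controls, which could itself affect their salt behaviour a little; neutral wording limits this.

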### Study sample

To calculate sample size, the following formula will be used:

$$ N=\frac{{\left({U}_{\alpha }+{U}_{\beta}\right)}^2\times 2P\left(1-P\right)}{{\left({P}_1-{P}_2\right)}^2} $$

where α = 0.05, β = 0.1, and then U_0.05_ = 1.96, U_0.1_ = 1.28. According to a previous study in China, the proportion of daily per capita salt consumption ≤6 g was 37.91% and the proportion increased to 45.91% after using salt-control spoons in participating households [16]. Thus, in this study, the increase in low salt consumption (≤6 g/d) with SALTCHECKER from about 38% (*P*_*1*_) to some 46% (*P*_*2*_), *P* = (*P*_1_ + *P*_2_)/2 = 0.42 was assumed. The sample size is calculated to be 799 cases. According to some similar salt-limiting trials, the dropout rate was 0.5–5% [18, 40–42]. And sampling error and invalid questionnaires may be 10–15%. Therefore, it was assumed 10–20% should be added on the basis of the estimated sample size, so 879–959 participants will be needed. The data of the tabulation on the 2010 population census of the People’s Republic of China (No. 1) indicated that the average household size in Chongqing is 2.70 (person/household) [43]. Therefore, 300 households’ main cooks in each of the intervention group and control group will be investigated in this study.

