### Recruitment

The households will be recruited from Chongqing, China. The study will be advertised in cooperative communities. The following strategies will be used sequentially until the desired sample size is achieved: (1) posters and project leaflets will be distributed; (2) advertisements will be circulated on social media, such as WeChat and Weibo platforms; (3) the project will be presented in the community by project manager or project members in the form of health seminars; and (4) the use, function and advantages of the SALTCHECKER will be demonstrated on-site.

Inclusion criteria: (1) the household’s main cook (involved mainly in household cooking); (2) plan to be living in Chongqing, China for at least 6 months; (3) own a mobile phone (iOS or Android) with Internet access; (4) and agree to have the WeChat mini programme on their mobile phones.

Exclusion criteria: (1) currently using a self-monitoring system or device to track or log living behaviour in household members; (2) having been involved in other salt experiments in household members; and (3) prior history of cognitive or verbal impairments or other diseases that may impact on study participation.

Interested household main cooks or their household members who are already using a self-monitoring system or tracking device will be excluded to avoid the potential confounding effect. The reason is that popular health apps or tracking device frequently implements various behavioural change strategies, which may affect participants’ behaviour.

On the basis of a computer-generated list in the statistical software IBM SPSS version 22.0 (IBM Corp, Armonk, NY, USA), we will randomly select 600 households’ main cooks (who meet the above-mentioned inclusion criteria) from the available household main cooks in the project database. Written informed consent will be collected from all the participants.

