#### Questionnaire survey

A self-administered questionnaire will be designed based on the local and international literature to assess the salt consumption-related KAP of the household’s main cook. The questionnaire will be sent to the household’s main cook through the salt-limiting WeChat mini programme. After the pre-investigation, the reliability and validity of the questionnaire will be tested. The questionnaire will include the following three parts:
Knowledge of salt consumption, such as the daily recommended intake of salt, high-salt diet hazards, recognition of seasonings and food with high sodium, etc. The knowledge of salt consumption is measured (0 = no, 1 = yes, 0 = do not know), and some items require reverse coding.The attitude of salt consumption, such as the attitude to salt-limiting or low-salt diets, awareness and intention of choosing a low-salt diet, etc. will be assessed using the 5-point Likert scale (1 = strongly disagree to 5 = strongly agree) questions.The practice of salt consumption, such as the use of low-sodium salt, proper use of salt-limiting spoons, selection of low-salt food, requiring low-salt food in restaurants, selection of food based on the nutrient list, etc. will be measured using the 5-point Likert scale (1 = strongly disagree to 5 = strongly agree) questions.

A total score will be calculated for the above items, and a high score will represent a high KAP.

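### Adherence rewards include a graduated salt spoon and a smart watch, which are not neutral, and the article does not make clear which arm receives them

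*Protocol article*

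**What the plan says.** The second limitation in the *Discussion* is that "we cannot ensure that all household main cooks will persist in receiving the intervention on the salt-limiting WeChat mini programme". Among the remedies it lists: "we will provide some reward (e.g. a salt spoon with a scale, a sphygmomanometer and a smart watch) to promote adherence". The rewards are for daily use of the system, so they fall within the six months in which outcomes are measured.

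*Data of the daily added salt intake integrity*, under *Quality control*, also mentions rewards: "A certain reward will be given to the households’ main cooks who actively participate in the programme every month". It names neither an arm nor an item.

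Three other places bear on the choice of items:

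- *Study sample* bases the planning effect on an earlier study in which "the proportion increased to 45.91% after using salt-control spoons in participating households", and then assumes "the increase in low salt consumption (≤6 g/d) with SALTCHECKER from about 38"% to about 46%.
- *Questionnaire survey* lists "proper use of salt-limiting spoons" among the practice items of the KAP score, and *Primary outcomes* names KAP as primary.
- *Recruitment* excludes households "currently using a self-monitoring system or device to track or log living behaviour in household members". The reason given is that such products may themselves change behaviour and so confound the comparison.

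**The concern.** A reward for adherence should keep people in the trial without acting on the outcome. A graduated spoon acts on the same behaviour as SALTCHECKER, namely the amount of salt added at the stove. The *Background* lists salt-restricting tools among the common salt reduction initiatives, so the protocol itself regards them as interventions. The spoon also touches a scored item of a primary outcome. A smart watch brings in, after randomization, the kind of influence that the entry criterion was meant to keep out.

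What is at stake is attribution. If the gifts follow use of the mini programme's intervention content, intervention households will receive more of them, and a difference between arms would be the effect of SALTCHECKER plus spoon. Analysis could not readily separate the two, because receipt of the gift would depend on use of the system after randomization.

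**Working it through.** **1. The plan's own figure.** *Study sample* gives P1 = 0.38, P2 = 0.46, P = 0.42, U values 1.96 and 1.28:

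N = (1.96 + 1.28)² × 2 × 0.42 × 0.58 / 0.08² = 799.1

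The stated 799 reproduces. The formula returns a number per group. It is close to the 300 × 2.70 = 810 household members expected per arm, so 799 per arm is used below.

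**2. The spoon figure beside the design effect.** Cited spoon study: 45.91 − 37.91 = 8.00 points. Assumed for SALTCHECKER: 46 − 38 = 8 points. The two are equal because the second was taken from the first.

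**3. What unequal or equal rewards could do.** Illustrative assumptions, none of them in the documents: a share f of an arm receives and uses a spoon; each user gains the cited 8 points; observations are independent. With d = p2 − p1 and p̄ the mean of the two proportions,

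power = Φ{ [d√n − 1.96√(2p̄(1−p̄))] / √(p1(1−p1) + p2(1−p2)) }, n = 799

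*(a) Spoons in the intervention arm only, SALTCHECKER truly without effect.* Control 38%, intervention 38% + 8f. Example, f = 50%: d = 0.04, p̄ = 0.40, giving (1.131 − 1.358)/0.692 = −0.328 and Φ = 0.37.

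| f | spurious difference | chance of a significant result favouring SALTCHECKER |
|---|---|---|
| 25% | 2 points | 13% |
| 50% | 4 points | 37% |
| 75% | 6 points | 68% |
| 100% | 8 points | 90% |

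The nominal figure in that direction is 2.5%.

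*(b) Spoons in both arms, adding nothing on top of SALTCHECKER.* Control 38% + 8f, intervention 46%.

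| f | true contrast | power |
|---|---|---|
| 0% | 8 points | 90% |
| 10% | 7.2 points | 83% |
| 25% | 6 points | 68% |
| 50% | 4 points | 36% |

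*(c) Spoons for everyone in both arms, effects fully additive.* 46% against 54%: power 89%.

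Cases (b) and (c) bracket equal distribution. The loss depends on how far the two effects overlap.

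**4. KAP.** Spoon use is one of five practice examples, each on a 1 to 5 scale, within a total over three domains. If it is a single item, it can move a respondent's total by at most 5 − 1 = 4 points. The document gives no standard deviation for the total, so the shift cannot be standardized. An equal shift in both arms leaves the between-arm comparison intact; an unequal one does not.

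**5. Who gets the rewards.** The *Discussion* offers them as a cure for poor persistence with the intervention delivered by the mini programme, and *Control group* gives controls the weighing function only. That points to the intervention arm. *Quality control* rewards any main cook who takes an active part, and the *Discussion* sentence itself goes on to speak of participants in general. That points to both arms. The text does not settle it.

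**The case against.** The strongest reply is that the bias is conditional. No sentence says that the arms are rewarded differently. All participants must agree to have the mini programme, and the KAP questionnaire is sent through it, so mentioning it does not by itself single out the intervention arm. The items are examples in a paragraph on limitations, and a full protocol may set out the reward scheme. This stands as to direction and size. It does not remove the fact that the article names a salt-reduction tool as a reward during follow-up.

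Four stronger readings are tempting, and the documents do not support them:

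- *The spoon alone is worth 8 points, the whole effect of SALTCHECKER.* The source figure is worded as a rise after spoon use. Whether that study had a control group or accompanying education cannot be seen. It also concerns the proportion at or below 6 g/d, whereas the primary outcome is daily added salt intake. The *Background* adds that salt-limiting spoons are awkward to use, so receiving one is not the same as using it.
- *Giving spoons to both arms must weaken the trial.* Case (c) shows almost no loss if the effects add.
- *KAP is biased whichever arm is rewarded.* An equal shift cancels in the comparison.
- *The smart watch breaches the exclusion criterion.* The criterion covers current use at entry and does not name watches. The conflict is with its stated reason only, and no effect of a watch on added salt is shown.

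Treating the rewarded spoon and the cited salt-control spoon as the same kind of tool is an inference, though a close one.

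**Conclusion.** The point holds in a limited form. As written, the plan offers an active salt-reduction tool, and a device type whose influence on behaviour it sought to avoid, as rewards for using the system. It does not make clear that both arms are treated alike.

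If rewards reach mainly the intervention arm, the spoon is confounded with SALTCHECKER in its favour: a spurious 2 to 8 points, and a 13% to 90% chance of a false positive finding, as f runs from 25% to 100%. If they reach both arms equally, the between-arm comparison is still fair, and the contrast shrinks only as far as the effects are less than additive: power between 36% (no added effect, f = 50%) and 89% (full additivity, f = 100%).

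These figures illustrate scale and are not forecasts. They rest on the cited 8 points being causal, on an uptake that the documents do not give, on the sizing outcome and not the primary one, and on independent observations although household members share one salt container.

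**What to change.** Replace the salt spoon and the smart watch with rewards unrelated to salt or behaviour tracking, such as phone credit or ordinary household goods. State in *Quality control* that both arms are rewarded on the same schedule and by a criterion that both can meet alike, for example completing the questionnaires and keeping the checker in use, and bring the *Discussion* into line with it. Hold any salt-related gift until after the 6-month assessment. The sphygmomanometer need not be removed if it is given equally in both arms; the plan encourages blood pressure data from participants with hypertension and foresees a possible blood pressure analysis.

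The cost is a different choice of gifts and a sentence or two of protocol text. The downside is that the gifts may be slightly less attractive.
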